#### Stopping study drug

Because of the risk of corticosteroid-induced adrenal suppression, the study drug must be stopped in a carefully controlled manner. Few good-quality data are available to enable prediction of the degree of adrenal suppression that occurs with corticosteroid therapy. Therefore, conventional rules for management of corticosteroid withdrawal will be followed for study patients. Tapering the dose of corticosteroids reduces the risk of adrenal suppression. Study drug should only be stopped immediately in two circumstances:if the patient has received four or fewer doses of the study drug, orif the study drug is being replaced by other corticosteroid therapyIn all other circumstances, study drug will be stopped by using dose tapering by moving the patient’s treatment forward on the dosing schedule, as illustrated below: (for example, if the patient is in week 3 of treatment, he or she should be moved immediately onto the week 4 dose, and then continue treatment as per the dose-tapering schedule with weekly reductions in the treatment dose) (Figure 4).

**Figure 4 Fig4:**
[figure not shown]
**Dose tapering in the event of stopping study drug.**

Any changes in patient’s medication must be recorded on the CRF and on the concomitant medication form.

#### Indications for stopping study drug/placebo

The main indication to stop the study drug is if the patient develops a condition for which there is good evidence that steroids are beneficial and should be prescribed. Examples of this are as follows:**Tuberculous meningitis:** Dexamethasone has been demonstrated in a large randomised controlled trial to reduce the risk of death [10]. If a patient develops TB meningitis, the study drug should be stopped, and the patient should receive the appropriate dosage of steroids according to the severity of the disease. This does not necessitate unblinding of treatment allocation.**Intracranial space-occupying lesion with mass effect:** For example, a primary brain tumour such as CNS lymphoma. Space-occupying lesion with mass effect is generally considered to be an indication for steroid therapy. A typical dose would be dexamethasone, 4 mg, 4 times daily. The study drug should be stopped in all patients, and the patient should receive corticosteroid treatment as per local guidelines. This does not necessitate unblinding of treatment allocation.**Note**: a suspected cryptococcoma is not an indication to alter the study drug; we do not know whether dexamethasone is indicated in this case, and the study is testing this indication.**Severe pneumocystis pneumonia (PCP):** All patients in the study must receive PCP prophylaxis with co-trimoxazole; this reduces the risk of developing PCP. However, PCP may still occur. Microbiologic confirmation of PCP is not always possible, and the diagnosis is often made on clinical grounds. The chest radiograph typically shows bilateral interstitial, often perihilar, shadowing. The differential diagnosis of this appearance includes bacterial pneumonia and acute respiratory distress syndrome (ARDS) due to cryptococcosis. The gold standard for diagnosis of PCP is to demonstrate the presence of *Pneumocystis jirovecii* in bronchoalveolar lavage washings or in induced sputum samples. Severe PCP is confirmed when there is a typical clinical syndrome is present AND the arterial blood oxygen partial pressure (pO_2_) is less than 70 mm Hg (FiO_2_ ≥ 20%). Prednisolone (40 mg twice daily for 5 days, 40 mg once daily for 5 days, followed by 20 mg/day for 11 days), in combination with high dose co-trimoxazole, has been shown to reduce the risk of death from severe PCP [41]. Where arterial blood gas measurement is not available, diagnosis of severe PCP should be made in accordance with local guidelines. In any patient in whom the diagnosis of severe PCP is made, the study drug must be stopped immediately, and the patient treated with prednisolone in conventional doses, and high dose co-trimoxazole as per local guidelines. This does not necessitate unblinding of treatment allocation.

Any changes to study medication will be recorded in the case-record form.

#### Unblinding

Unblinding means revealing the identity of the study treatment (that is, dexamethasone or placebo). Treatment allocation should be unblinded only if knowing the treatment that a patient has been allocated will result in a change in the patient’s management. The need to unblind is likely to be rare during the study. Unblinding a patient’s treatment allocation does not enable us to tell if a particular adverse event is due to the investigational agent; that conclusion can be drawn only with an analysis of all available data, either at an interim safety analysis (which is done by the independent data and safety-monitoring board) or after the final analysis of the study.

#### Process for unblinding

The decision whether to unblind should be discussed with the lead country investigator or the principal investigator, when possible. Unblinded treatment allocation should be held securely at each site and be available at all times. The responsibility to approve unblinding will be assigned to dedicated staff at each site. Access to treatment allocation should be given only with the approval of one of these dedicated staff. Unblinding will be documented in the case-record form.

### Data on concomitant medications

At each visit, information on other medications, including start dates and reason for taking them, will be documented in the case-record forms.

### Withdrawal from the trial

Patients may voluntarily withdraw from the trial for any reason. If this occurs, the patient will be referred to standard clinical care facilities. The patient’s withdrawal from the trial will not affect the access to the best standard of care within the local health system. With the agreement of the patient, clinical and laboratory assessment should be performed and recorded at the time of withdrawal. Patients may also decide to stop study treatment without withdrawing from the study, in which case, treatment will be adjusted as described later, and follow-up will continue as per the study schedule.

Provided no more than 4 days of study drug have been administered, if a patient wishes to withdraw, the study drug can be stopped immediately. If a patient has received 5 or more days of study drug, then it is possible that adrenal suppression has occurred, and the dose of dexamethasone should be tapered. Thus, if a patient wants to withdraw from the study, and has received 5 or more days of study drug, then the withdrawal phase of steroid dosing will be started immediately; the patient will be switched to the next dexamethasone dose in the steroid-dosing sequence. For example, if on day 16, a patient wants to leave the study, then he or she will be immediately switched to the next phase of steroid/placebo dose (3 mg/day), and the treatment tailed off according to the treatment schedule (Table 4). This continuation of treatment after withdrawal will be fully explained in the informed-consent form. Follow-up will be according to clinical need. All patients in the study will be provided with steroid information cards in their own language. These will detail the need to reduce the dose gradually if they are to be stopped, and to inform other health care workers that they are taking dexamethasone, should they require treatment from a health care worker not involved with the trial. If the patient has an unscheduled period off treatment or not in follow-up, this should be recorded in the case-report forms.

## Definition and assessment of adverse events

### Definition of adverse events

An adverse event (AE) is any undesirable event that occurs to a study participant during the course of the study, regardless of whether that event is considered related to the study drug. An AE can, therefore, be any unfavourable and unintended sign (including an abnormal laboratory finding, for example), symptom, or disease temporally associated with the study drug, whether or not considered related to the study drug.

Examples include the following:

An increase in severity or frequency of a preexisting abnormality or disorder (events that are marked by a change from the participant’s baseline/entry status)All reactions from sensitivity or toxicity to study drugInjuries or accidents (for example, for a fall secondary to dizziness, “dizziness” is the event and the injury secondary to the fall is the “outcome”)New clinically significant abnormalities in clinical laboratory values, physiological testing, or physical examination.

Stable chronic conditions, such as arthritis, which are present before clinical trial entry and do not worsen are not considered AEs and will be documented in the subject’s clinical chart as medical history.

Clinical or laboratory events are considered adverse events only if they occur after the first dose of study treatment and before the patient completes trial participation. (See later for reporting of adverse events.)

### Definition of serious adverse events

An AE is considered to be "serious" if it results in one of the following outcomes

Death,Life-threatening event (the subject was at immediate risk of death at the time of the event; it does not refer to an event that hypothetically might have caused death if it were more severe),Inpatient hospitalisation or prolongation of existing hospitalisationPersistent or significant disability/incapacity (a substantial disruption of a person's ability to conduct normal life functions),Congenital anomaly/birth defect,Important medical event that may not be immediately life-threatening or result in death or hospitalisation but may jeopardise the patient or may require intervention to prevent one of the other outcomes listed in the earlier definition.

### Definition of unexpected serious adverse events

Unexpected serious adverse events are untoward medical events that fit one or more of the previously explained criteria for SAEs and that are not considered a part of normal clinical progression of disease or an expected drug reaction. Any event that becomes of concern to the investigators or study doctors during the course of the trial may be reported as a USAE.

### Assessment of adverse events

Adverse events will be defined according to the Common Terminology Criteria for Adverse Events (CTCAE) definitions: http://ctep.cancer.gov/protocolDevelopment/electronic_applications/ctc.htm. New AIDS-defining events will be defined according to the revised CDC criteria modified for this trial (see Table 5, and Appendix 6). In the event that an adverse event is not described within the CTCAE definitions, or a new AIDS-defining event, as defined in Table 5, the following generic severity grading will be used:

**Grade 1 Mild;** asymptomatic or mild symptoms; clinical or diagnostic observations only; intervention not indicated.

**Grade 2 Moderate;** minimal, local, or noninvasive intervention indicated; limiting age-appropriate instrumental Activities of Daily Living (ADLs)*.

**Grade 3 Severe or medically significant but not immediately life-threatening;** hospitalisation or prolongation of hospitalisation indicated; disabling; limiting self-care ADL**.

**Grade 4 Life-threatening consequences;** urgent intervention indicated.

*Instrumental ADLs refer to preparing meals, shopping for groceries or clothes, using the telephone, managing money, and so on.

**Self-care ADLs refer to bathing, dressing and undressing, feeding self, using the toilet, taking medications, and not bedridden.

Details on the grading of specific adverse events can be found in Appendix 6. [Note: “Life-threatening” as a severity grade is not necessarily the same as “life-threatening” as a “serious” criterion used to define a serious adverse event. The former is a “potential” threat to life, and the latter is an “immediate” threat to life.]

A **laboratory abnormality** must be recorded as a clinical adverse event only if it is associated with an intervention. Intervention includes, but is not limited to, discontinuation of a current treatment, dose reduction/delay of a current treatment, or initiation of a specific treatment. In addition, any medically important laboratory abnormality may be reported as an adverse event at the discretion of the investigator. This would include a laboratory result for which no intervention is needed, but the abnormal value suggests a disease or organ toxicity. Laboratory events will be graded according to CTCAE definitions.

If clinical sequelae are associated with a laboratory abnormality, the diagnosis or medical condition should be reported as the adverse event (for example, renal failure, haematuria), not the laboratory abnormality (for example, elevated creatinine, urine RBC increase).

## Recording and reporting of adverse events and protocol violations

### Adverse event recording

Grade 3 and 4 adverse events will be recorded in the case report form and entered into the study database. Grade 1 and 2 events will not be recorded, because in a severe disease such as CM, the number of low-grade adverse events is likely to be high, representing a large reporting burden, which may affect the quality of recording and reporting of more important grade 3 and 4 adverse events.

### Adverse event reporting

Serious adverse events and serious unexpected adverse events will be **reported** to the Principal Investigator within 7 days of occurrence, or sooner, according to local requirements. The Principal Investigator will report all unexpected serious adverse events to the DMEC within 10 days of occurrence. Unexpected serious adverse events will be reported to the responsible ethical committees within 10 days of occurrence, or as required by the committee.

### Protocol violations

Protocol violations are events that contradict or omit protocol instructions. Violations that compromise patient safety or the integrity of trial data will be recorded and reported to the responsible Ethics Committees, as required by the regulations of each Committee.

## Statistics

### Sample size and power considerations

The trial is powered for the primary end point (that is, overall survival during the 10-week follow-up period).

Few data exist on which to estimate the potential effect size of dexamethasone on mortality from CM. We have based our estimate of the effect size on data from tuberculous meningitis, which shares clinicopathologic features with CM. In a large RCT of dexamethasone to treat tuberculous meningitis in Vietnam, the hazard ratio (HR) for death was 0.69 at 9 months in favour of dexamethasone [25]. Most of this effect occurred during the first 3 months of treatment. The dose of dexamethasone we will test is the same as that used in that trial. Additionally, in a study of dexamethasone in bacterial meningitis in Vietnam, the HR was 0.43 in patients with microbiologically confirmed disease, and 0.59 in a study based in Europe, again in favour of dexamethasone [34, 35]. These analyses were all based on the intention-to-treat principle (including noncompliant patients), and it seems sensible to expect a similar rate of noncompliance in our study. Therefore, we believe a target hazard ratio of 0.7 in favour of dexamethasone to be reasonable for our trial.

To detect such a risk reduction of 30% with 80% power at the two-sided 5% significance level, a total of at least 247 deaths must be observed. Based on historical data and consultation with principal investigators from all study sites, the 10-week mortality risk in the control group is expected to be between 30% and 50% [38], and the target hazard ratio of 0.7 corresponds to absolute risk reductions in mortality from 30% to 22%, or from 50% to 38%. Assuming an overall 10-week mortality of at least 30% in our study population, recruitment of 824 patients is sufficient to observe the target number of deaths. Allowing for some loss to follow-up, the total sample size for this study is 880 patients.

A major aim of this trial is to generate robust evidence across both continents. To achieve this goal, we aim to recruit roughly similar numbers of patients from each continent.

Event-driven stopping of the trial after 247 observed deaths is not foreseen even if this should occur prior to recruiting 880 patients. Thus, the study will be conservatively powered if the study mortality is larger than 30%. For example, if overall mortality was around 50% and 412 deaths were observed during the study, power would increase to 95% for a true hazard ratio of 0.7 and to 83% for a true hazard ratio of 0.75.

### Analysis

#### Analysis of the primary end point and 6-month mortality

The analysis will be based on a stratified Cox proportional hazards model allowing for separate baseline hazards for each continent (Asia or Africa) and treatment allocation as the only covariate. The stratification is based upon the expectation of different mortalities in the control arm by continent but similar (relative) effects of the intervention across continents. The proposed test is essentially equivalent to using a stratified log‒rank test to compare the two treatment arms. We prefer to use the Cox model as it automatically provides treatment effect estimates and confidence intervals in addition to the *P* value.

In a second stage, overall survival will be modelled by using the Cox proportional hazards regression model with stratification by continent and the following covariates (in addition to the treatment group): country, baseline fungal load, Glasgow coma score less than 15, and ARV status at study entry (ARV naïve or experienced).

Potential heterogeneity of the treatment effect will be assessed based on appropriate interaction (likelihood ratio) tests and the following predefined subgrouping variables:

ContinentCountryIDSA indications for steroid treatment at baseline (cryptococcoma with mass effect, acute respiratory distress syndrome or IRIS: yes or no)Glasgow coma score <15 (yes or no)Naïve to ARVs at study entry versus on ARVS at study entry

All Cox regressions and sub-group analyses will be performed for the primary end point (10-week survival) as well as for 6-month survival. Kaplan-Meier plots and explicit survival estimates at 10 weeks and 6 months of follow-up will also be calculated for the full populations and for each continent separately.

#### Analysis of secondary end points

##### Neurologic disability

The disability score at week 10 and month 6 of follow-up is defined as the higher (worse) of the “simple question” and the Rankin score assessed at that time point and will be categorised as good outcome, intermediate disability, severe disability, or death (in case the patient died before the respective time point) as previously described [10] (also see Table 1). The proportion of patients with a good outcome will be compared between the two arms with a logistic regression adjusted for continent (in addition to the treatment arm). Patients lost to follow-up will be analysed according to their last recorded disability status. If the rate of patients lost to follow-up exceeds 10%, we will also perform an alternative analysis based on multiple imputation of missing values.

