**The modified rankin scale**		
**Grade**	**Description**	
0	No symptoms	
1	Minor symptoms not interfering with lifestyle	
2	Symptoms that lead to some restriction in lifestyle, but do not interfere with the patients’ ability to look after themselves	
3	Symptoms that restrict lifestyle and prevent totally independent living	
4	Symptoms that clearly prevent independent living, although the patient does not need constant care and attention	
5	Totally dependent, requiring constant help day and night	

Grade 0: Good outcome, Grade 1 or 2: Intermediate outcome, Grade 3-5: poor outcome.

Disability is an expected consequence of cryptococcal meningitis, including blindness, deafness, and other focal neurological deficits. In addition to reduced death rate, patients receiving dexamethasone may also have lesser (or higher) rates of these disabilities. The Rankin score and the Two Simple Questions are well-validated measures of the degree of disability in stroke survivors, and have been used frequently to measure disability after neurologic infections.

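### The four-level disability outcome is compared only as good versus the rest, so the planned test cannot see shifts among intermediate disability, severe disability and death

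*Protocol article*

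**What the plan says.** The section on neurologic disability (Analysis of secondary end points) says that the score at week 10 and at month 6 "is defined as the higher (worse) of the “simple question” and the Rankin score". It is then placed in one of four categories, the worst being death. Table 1 sets the Rankin bands: "Grade 0: Good outcome, Grade 1 or 2: Intermediate outcome, Grade 3-5: poor outcome". On the simple questions, a patient reaches the good level only by needing no everyday help and having no other remaining problem.

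The only between-arm comparison given for this outcome is: "The proportion of patients with a good outcome will be compared between the two arms with a logistic regression adjusted for continent". No second cut and no ordinal model is named.

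The text under Table 1 gives the purpose. Apart from any effect on death, "patients receiving dexamethasone may also have lesser (or higher) rates of these disabilities".

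Survival has its own analysis: stratified Cox models for 10-week and 6-month survival, with Kaplan-Meier plots and survival estimates (Analysis of the primary end point and 6-month mortality).

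**The concern.** The scale is ordered, but the test uses only its top boundary. Because the worse instrument counts, the good group excludes even Rankin grade 1, where symptoms are slight and daily life is unaffected. That patient is scored like one who is totally dependent or has died.

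Two movements are invisible to this test. One is a death averted into survival with intermediate or severe disability, which is where part of a mortality effect could land. The other is a worsening of survivors from intermediate to severe disability. The protocol asks about disability in either direction, and the second movement is the harm that a reader would look for in this end point. The Cox analyses show whether patients live, but not in what functional state.

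**Working it through.** **The plan's own figures.** The sample size section states: "To detect such a risk reduction of 30% with 80% power at the two-sided 5% significance level, a total of at least 247 deaths". With 1:1 allocation, deaths = 4(1.960 + 0.842)² / (ln 0.7)² = 246.8, so 247. Then 247 / 0.30 = 823.3, so 824 patients. Treated mortality at a hazard ratio of 0.7 is 1 − 0.70^0.7 = 22.1%, or 1 − 0.50^0.7 = 38.4%. All agree with the protocol. It gives no power or expected distribution for disability, so every survivor split below is an assumption.

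**Inputs.** There are 880 patients, 440 per arm, with a two-sided 5% level and no dropout or continent adjustment. Splits are written good/intermediate/severe/death, in percent.

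**1. Movement below the good level.** If the proportion good is the same in both arms, the good-versus-rest test rejects at alpha, 5%, whatever happens below. This needs no assumed split.

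As an example, take a control split of 25/25/20/30 and a dexamethasone split of 25/15/30/30.
- Good versus rest: 25% in both arms, so 5% power.
- Good or intermediate: 50% versus 40%. Null SE = √(0.45 × 0.55 × 2/440) = 0.0335. Alternative SE = √((0.25 + 0.24)/440) = 0.0334. Power = Φ[(0.10 − 1.96 × 0.0335)/0.0334] = Φ(1.03), about 85%.

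**2. Power of the two approaches.** The ordinal test is the tie-corrected Wilcoxon test, which is the score test of the proportional-odds model. Values come from simulation with 6,000 replicates; large-sample formulas agree to about one point.

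| Scenario | Control 25/25/20/30: good vs rest / ordinal | Control 15/30/25/30: good vs rest / ordinal |
|---|---|---|
| Deaths 30% to 22.1%, those saved spread like control survivors | 16% / 56% | 11% / 56% |
| Same fall in deaths, those saved become intermediate or severe | 5% / 36% | 5% / 43% |
| Common odds ratio 1.45 | 70% / 87% | 55% / 87% |
| 10 points move from intermediate to severe, deaths unchanged | 5% / 23% | 5% / 32% |

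**3. Information kept under a common odds ratio.** Relative efficiency = 3p(1 − p) / (1 − Σpᵢ³), with proportions averaged over the arms and p the proportion good. For control 25/25/20/30 and odds ratio 1.45, the averages are 0.288/0.258/0.190/0.264. This gives 3 × 0.288 × 0.712 / (1 − 0.066) = 0.66. The split 15/30/25/30 gives 0.47, and 35/20/15/30 gives 0.79.

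**4. Wider range.** Choose the common odds ratio to match the targeted fall in deaths: (0.30/0.70)/(0.221/0.779) = 1.51 at 30% mortality, and 1.60 at 50%. Total N for 80% power, ordinal versus binary:

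| Control survivors who are good | 30% mortality | Kept | 50% mortality | Kept |
|---|---|---|---|---|
| 10% | 610 vs 2392 | 26% | 483 vs 2440 | 20% |
| 20% | 602 vs 1334 | 45% | 480 vs 1322 | 36% |
| 35% | 594 vs 908 | 65% | 477 vs 856 | 56% |
| 50% | 609 vs 772 | 79% | 482 vs 684 | 70% |
| 70% | 673 vs 746 | 90% | 503 vs 592 | 85% |

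The loss is thus about 10% to 74% at 30% mortality and 15% to 80% at 50%. It exceeds half only when the good share among control survivors falls below a value lying between 20% and 35%.

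**The case against.** Five points can be made for the plan.

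- **The test is valid and prespecified.** It is easy to interpret, it serves a secondary end point for which no power is claimed, and no stated figure is wrong. This stands.
- **Survival is not lost.** A reader might infer that a patient saved from death into minor symptoms counts for nothing in the trial. That is true only inside this one comparison; the Cox analyses count that patient fully. This stands.
- **Much of the ordinal gain re-tests mortality.** In the first two scenarios of the power table the only effect is averted deaths. A plain comparison of deaths there has about 76% power, more than the ordinal test's 56% and 36%. This stands, and it limits what those rows show.
- **An ordinal main analysis can hide opposite shifts.** Suppose control is 25/25/20/30 and dexamethasone is 19/25/33.9/22.1: fewer deaths, but also fewer good outcomes. Good versus rest has about 58% power and the ordinal test about 8%. This stands, and it argues against replacing the planned comparison.
- **Other analyses capture morbidity.** Visual deficit, new neurologic event or death, and the quality-of-life and disability weights in the economic evaluation do so in part. None of them compares functional dependence between the arms, so the gap remains.

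It can also be said that a table of the four levels is ordinary analysis-plan detail. That is fair for the table alone, but the protocol does name the comparison, and the one it names stops at the top boundary.

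**Conclusion.** The point holds as a limitation of the specified comparison. Good versus rest has no power beyond alpha for shifts among intermediate disability, severe disability and death, and this follows from the definition alone. It includes a worsening of survivors from intermediate to severe, which bears directly on the protocol's stated question.

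The size of the efficiency loss is not fixed by the documents. Under the three assumed splits the binary cut keeps 47% to 79% of the ordinal information; over the wider range the loss is about 10% to 80%. These figures assume proportional odds and an unstated distribution of disability among survivors.

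A reader might go further and conclude that most of the information on disability and survival is thrown away. The documents do not support that. It would need a small good group, which the strict definition makes plausible but no figure establishes, and survival is analysed separately. Nor do they show that the ordinal model should displace the planned comparison, since each can miss what the other detects. This is a cheap improvement, not an error that invalidates the analysis.

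**What to change.** Keep the prespecified good-outcome comparison. At week 10 and month 6, add:

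1. the number and proportion of patients in each of the four categories, by arm;
2. odds ratios with confidence intervals, adjusted for continent, at each cut: good; good or intermediate; alive;
3. a supporting proportional-odds model over the four levels, adjusted for continent. State that it is read together with the cut-specific odds ratios, because opposite shifts can cancel and part of its effect reflects mortality.

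The cost is wording and analysis time; no new data, visits or patients are needed. The downside is a few more secondary estimates and a common-odds assumption, which the cut-specific results check.
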